## 13 Statistical Considerations

Patients satisfying eligibility requirements will complete a dietary questionnaire prior to randomization.

Patients will not be taking lycopene or omega-3 supplements, but other dietary sources of tomato lycopene or fish oil could possibly influence the assessment of outcome for this study. For example, it might be that an excess of tomato-consuming patients would be placed in the control arm, confounding the assessment of gene expression in response to lycopene. Therefore, patients will be stratified into four groups (low tomato/low fish, low tomato/high fish, high tomato/low fish, and high tomato/high fish) and block-randomized to placebo, lycopene, or fish oil, within these strata. This will avoid the chance occurrence of confounding due to usual intake of fish or tomato products (e.g. unbalanced patient features among the study arms). Cutoffs for the baseline dietary strata are based on the medians of intake from a **completed** independent pilot study on 96 prostate cancer patients from the source population at the UCSF Mt. Zion Cancer Center, who completed the Willett Semi-Quantitative Food Frequency Questionnaire. The median for total tomato consumption was 4 servings/week; for fish consumption it was two servings/week.

We will assess changes in serum lycopene and omega-3 fatty acid pre- and post-intervention to assess compliance and the physiologic significance of the supplementation doses.

For our primary analysis, changes in gene expression for each of the two nutrient interventions will be compared with that of the control arm. The two intervention arms will not be compared with each other. The primary outcome measure will be at least a two fold up decrease in gene expression of *IGF-1* or *COX-2* at three-months relative to the initial biopsy for a given patient (both normalized to levels of a control housekeeping gene,  *$\beta$ -glucuronidase*). To compare the intervention and control groups, we define an important difference to be a 40% difference in the proportion of patients on the intervention arm compared with the placebo arm who satisfy the primary outcome measure defined above (e.g. 20% in control vs. 60% in intervention showing at least a two-fold decrease in mRNA level). Fisher's exact test for proportions will be used to determine if *IGF-1* or *COX-2* mRNA levels are statistically significantly different between the groups.

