To evaluate the primary study aim, 29 patients will be randomized to the lycopene intervention, 29 to the fish oil intervention and 29 to the control arm. Analysis of 87 evaluable patients is sufficient to detect a 40% difference in the proportion of patients with a 2-fold decrease in *IGF-1* mRNA levels with lycopene or in the *Cox-2* gene with fish oil when compared with the control. The total accrual of 97 patients takes into consideration a 10% dropout rate by the time of the three-month biopsy. The level of significance for a directional test is set at .025 because the control group will be compared with each of the two intervention groups. The power of each test is set at 81% (nQuery).

Descriptive statistics (mean, confidence intervals, median, proportions) will be calculated to characterize the patients' baseline disease features (e.g. age, Gleason score, PSA) and self-reported nutritional dietary data within each arm. Differences between each of the intervention arms and the placebo arm will be assessed using a chi-square statistic for categorical variables, a t-statistic for continuous variables and the Mann-Whitney statistic for distributions. Estimates of the probability of remaining free of disease progression will be calculated using the Kaplan-Meier product limit method. The log rank test will be used to compare tumor progression between each supplement group and the control (Aim 1.5).

The randomized clinical trial design of this study limits the potential for confounding due to other factors, however this will be investigated by comparing the distribution of clinical parameters and other diet/lifestyle factors as well as changes after 3 months of study treatment among the three arms. Unequally distributed factors would only bias the results if they also

correlate with changes in gene expression. If necessary, the Mantel-Haenszel test for a stratified analysis would be performed in evaluating the primary study aim.

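### Two primary comparisons are each held at a fixed directional .025; if a one-sided .05 family-wise level is intended, Holm's procedure keeps it with more power (efficiency, not validity)

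*Protocol*

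**What the plan says.** The primary analysis in section 13 has two comparisons: lycopene against placebo for IGF-1, and fish oil against placebo for Cox-2. The protocol rules out a third: "The two intervention arms will not be compared with each other".

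The level is fixed in the same section: "The level of significance for a directional test is set at .025", with the reason "because the control group will be compared with each of the two intervention groups". The remaining design inputs are:

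- target difference: "20% in control vs. 60% in intervention showing at least a two-fold decrease in mRNA level"
- test: "Fisher's exact test for proportions will be used to determine if" expression of the two genes differs between groups
- evaluable size: "29 patients will be randomized to the lycopene intervention, 29 to the fish oil intervention and 29 to the control arm"
- accrual: "The total accrual of 97 patients takes into consideration a 10% dropout rate"
- power: "The power of each test is set at 81% (nQuery")

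The protocol mentions no step-down, ordering or passing on of level between the two comparisons.

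**The concern.** The stated reason makes .025 a multiplicity adjustment: a one-sided .05 halved over two tests. Under that rule the second comparison is still held to .025 after the first has been rejected. At that point only one null hypothesis is left, and a family-wise level of .05 would allow it to be tested at .05.

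What is at stake is a real effect of the second supplement being missed for want of a level that the error rate would have allowed. For example, suppose 6 of 29 placebo patients respond. Then 13 of 29 on a supplement gives a one-sided Fisher p of .046, and 14 of 29 gives .026. Both fail the fixed rule. Both would succeed under Holm if the other comparison had reached p ≤ .025.

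**Working it through.** **Inputs (protocol section 13).** Directional .025 per test; response 20% on placebo and 60% on supplement; 29 evaluable per arm; Fisher's exact test; 81% power; 10% dropout; two comparisons. The family-wise .05 is inferred as 2 × .025.

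**1. The plan's own sample size.**

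- Uncorrected formula: n = [z(.975)·√(2·0.4·0.6) + z(.81)·√(0.2·0.8 + 0.6·0.4)]² / 0.4² = (1.960·0.693 + 0.878·0.632)² / 0.16 ≈ 22.9.
- Continuity correction: (22.9/4)·[1 + √(1 + 4/(22.9·0.4))]² ≈ 27.65, so 28 per arm against 29 stated.
- Exact power of the one-sided Fisher test at 29 per arm is 83.0%, about 2 points above the stated 81%.
- Accrual: 87/0.9 = 96.7, so 97, as stated.

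The design therefore reproduces closely as one-sided .025 per test. A two-sided .025 Fisher test would have only 75.4% power at 29 per arm.

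**2. Fixed split against Holm, both supplements effective.** Exact enumeration of the one-sided Fisher test at 29 per arm, 20% v 60%, gives power a = 0.8301 at .025 and b = 0.8964 at .05. Treating the two comparisons as independent:

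| Power | Fixed .025 | Holm |
|---|---|---|
| Per comparison | a = 83.0% | a + (b − a)·a = 0.8301 + 0.0663·0.8301 = 88.5% |
| Both | a² = 68.9% | 2ab − a² = 1.4882 − 0.6891 = 79.9% |
| At least one | 1 − (1 − a)² = 97.1% | 97.1% |

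**3. Shared placebo arm.** The comparisons share their controls, so independence is an approximation. A simulation assumed a latent correlation of 0.5 to 0.99 between the two genes in placebo patients. Holm then gives 87.8% to 88.3% per comparison, and power for both rises from 70.0%–72.3% to 80.4%–81.7%. The conclusion does not depend on independence.

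**4. Smaller effects (assumed, both supplements).** Power for both rises from 50.9% to 64.7% at 20% v 55%, and from 32.8% to 46.6% at 20% v 50%.

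**5. Only one supplement effective.** The actual size of the Fisher test at a 20% response rate is .0106 at nominal .025 and .0222 at nominal .05.

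- Power for the effective supplement: 0.8301 + 0.0663·0.0106 = 0.8308, that is 83.0% to 83.1%.
- Error for the inert supplement, nominal: .025 + .025·0.8301 = .046, up from .025.
- Error for the inert supplement, actual Fisher size: .0106 + (.0222 − .0106)·0.8301 = .020, up from .011.

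**6. Neither effective.** Both procedures have the same family-wise error: nominally 1 − 0.975² = 4.94% for independent tests.

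**The case against.** The strongest reply is that nothing in section 13 is in error. The protocol states its level, gives a reason and powers each test at that level, and each test exceeds the stated 81%. That stands, and it makes this a refinement.

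Three further points also stand in part.

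- **The .05 is inferred.** The only level printed for a primary test is .025. If the sponsor means .025 as a ceiling for each test in its own right, Holm's second step is not available and the gain does not arise. The stated reason, two comparisons with one control, points to a split, but the sponsor must confirm it.
- **Power for both is not the plan's criterion.** The protocol sets power for each test. On that criterion the gain is 5.5 points, and only when both supplements work.
- **Holm is not free.** It nearly doubles the error for an inert supplement when the other one works, although the family-wise level holds.

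A reader might infer that the fixed split makes the analysis invalid, leaves the trial underpowered, or throws away part of the 5% in all circumstances. The protocol supports none of these. The split controls the error, the sample size reproduces, and with neither supplement effective almost the whole nominal 5% is used. The unused level appears only after one rejection. The conservatism of Fisher's test (actual size about 1.1% at nominal 2.5%) is a separate loss that Holm does not recover.

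The objection that such details belong in a statistical analysis plan carries less weight, because the protocol itself fixes .025 for each test.

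**Conclusion.** The point holds as an optional, cheap gain in efficiency. If a one-sided .05 is the intended family-wise level, Holm is never less powerful than the fixed split and needs no assumption about the dependence created by the shared placebo arm.

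The gain is 5.5 points per comparison and 11.0 points for both, given 29 evaluable per arm, 60% against 20% for both genes, one-sided Fisher tests and independent comparisons. There is no gain in the chance of at least one success, and next to none if only one supplement works. Validity and sample size are not in question.

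**What to change.** Confirm that a one-sided .05 is the intended family-wise level. If so, replace the sentence on the level, before unblinding, with: *The two directional comparisons are tested by Holm's procedure at a one-sided family-wise level of .05 (smaller p at .025; if significant, the other at .05).* Keep 81% as the minimum power per test, since the first step is unchanged.

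The cost is one sentence, with no added patients, biopsies or change of test. Two consequences should be accepted knowingly: the higher error for an inert supplement when the other works (nominal .025 to about .046), and the fact that simple 97.5% confidence bounds will no longer match every test decision. If the sponsor wants .025 as a ceiling for each test, keep the present rule and say so.

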### 4.6 Method of treatment assignment and blinding

Patients will be stratified prior to randomization based upon their dietary intake of tomato and fish. Four strata have been defined (low tomato, low fish; low tomato, high fish; high tomato,

low fish; and high tomato, high fish) using the results from a pilot study of 96 subjects. The cutoff for low vs. high tomato-product intake will be four servings/week; the cutoff for low vs. high fish intake will be two servings per week. Patients will be randomized from within each of the 4 strata to one of the 3 study regimens (placebo, lycopene or omega-3) with equal probability. This will ensure that there is a balance of patients based upon current dietary intake among the 3 arms. Treatment assignment will be balanced after every 9 patients are randomized within each stratum. Because the distribution by strata is unknown the block size is small to avoid an imbalance as the study approaches conclusion. As indicated each intervention arm will be compared with the placebo group so it is important to maintain a balance in baseline diet as to lycopene and omega-3 in each of the 3 study arms.

Data on usual intake in this trial will be assessed at baseline by the same dietary survey used in the pilot study.

In the control arm (arm 1), patients will maintain their usual diet and take placebos representing lycopene and fish oil. In the lycopene arm (arm 2), patients will take 30mg of lycopene and a placebo representing fish oil, in the omega-3 arm (arm 3), they will take 3g of fish oil daily, and a placebo representing lycopene.

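### Randomisation is stratified by diet but the primary test is not, and the stratified test is an undefined fallback that follows a look at arm differences including 3-month changes

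*Protocol*

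**What the plan says.** Protocol section 4.6 sets four strata, low or high tomato crossed with low or high fish: "Patients will be randomized from within each of the 4 strata to one of the 3 study regimens". Section 13 repeats that patients are "block-randomized to placebo, lycopene, or fish oil, within these strata" and gives the reason: "other dietary sources of tomato lycopene or fish oil could possibly influence the assessment of outcome for this study".

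For the primary comparison of each supplement arm with placebo, section 13 states: "Fisher's exact test for proportions will be used to determine if" the two target genes differ between groups. The strata are not mentioned. The design effect is "20% in control vs. 60% in intervention showing at least a two-fold decrease in mRNA level", with 29 evaluable patients per arm, a directional level of .025 per comparison and 81% power.

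Later in section 13, possible confounding is to be examined by comparing the arms on clinical parameters and other diet and lifestyle factors, "as well as changes after 3 months of study treatment among the three arms". The text notes that an unequally distributed factor would cause bias only if it were also correlated with change in gene expression. It then says: "If necessary, the Mantel-Haenszel test for a stratified analysis would be performed in evaluating the primary study aim".

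**The concern.** There are three problems, the last two more serious than the first.

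1. **Design and analysis do not match.** Diet was judged important enough to randomise on, yet the planned test ignores it. If diet predicts response, ignoring the strata makes Fisher's test more conservative than it need be. The fallback is introduced for factors other than the randomisation strata, so it may not use them either.

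2. **The data can choose the test.** The fallback has no trigger, no named stratifying variable and no rule for which result governs if the two tests disagree. The remark about correlation with gene expression sends the analyst to the outcome data to decide whether, and on what, to stratify.

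3. **Post-randomisation variables are not excluded.** Changes over three months of treatment can be effects of the supplement. The study table measures PSA, testosterone, serum IGF-1, serum lycopene and the omega-3/6 ratio at three months, and section 13 uses the lycopene and omega-3 changes to judge compliance and physiological effect. Stratifying on such a change can remove the effect under test, and the comparison is then no longer a randomised one.

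**Working it through.** **Inputs from the protocol.** 29 evaluable per arm; 20% against 60%; one-sided .025; 81% power; four strata with equal allocation (sections 4.6 and 13).

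**Assumed, because the protocol does not give them.** Stratum sizes of 8, 7, 7 and 7 per arm (sum 29), and the placebo response rate in each stratum.

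**Step 1: the plan's own figure.** The continuity-corrected two-proportion formula (20% against 60%, one-sided .025, 81% power) gives 28 per arm, against 29 stated. Exact enumeration for Fisher's test sums the binomial probabilities over all (x, y) with P(Y ≥ y | x + y) ≤ .025. It gives 82.3% power at 28 per arm and 83.0% at 29. The stated sample size is therefore reproduced, and it rests on an unstratified one-sided test.

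**Step 2: Fisher against the exact stratified test.** The stratified statistic is S, the sum over strata of responders on active treatment. Given the stratum totals, its null distribution is the convolution of four hypergeometric distributions; reject if P(S ≥ s) ≤ .025. Under the alternative, a common odds ratio is set so that the active arm responds at 60% overall. Both tests were enumerated exactly.

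| Assumed placebo rates in the four strata | Odds ratio | Power, Fisher | Power, stratified | Type I error, Fisher | Type I error, stratified |
|---|---|---|---|---|---|
| 20, 20, 20, 20% | 6.0 | 83.0% | 83.5% | 1.06% | 1.15% |
| 15, 15, 25, 25% | 6.3 | 83.6% | 84.7% | 1.00% | 1.14% |
| 8, 14, 23, 35% | 7.4 | 85.0% | 88.1% | 0.84% | 1.13% |
| 5, 10, 20, 45% | 9.5 | 86.2% | 91.4% | 0.61% | 1.09% |

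The weighted placebo rate is 19.5% to 20.0% in every row. As diet becomes more prognostic, Fisher's true error falls further below .025, while the stratified test stays near 1.1%.

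A second, simulated parameterisation spreads the stratum log-odds by up to ±1.5 and does not hold the overall rates fixed (they drift to about 25% against 58%). There Fisher has 62% power and the continuity-corrected Mantel-Haenszel test 72%, a gain of 10 points.

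**Step 3: the optional switch.** This is a simulation under no treatment effect, with 29 per arm and binary baseline factors each assumed to carry a log-odds ratio of 0.7. Success is declared if Fisher's test or any one-factor Mantel-Haenszel test reaches one-sided .025.

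| Candidate factors | Error, uncorrected Mantel-Haenszel | Error, continuity-corrected |
|---|---|---|
| 5 | about 3.8% | about 1.6% |
| 10 | about 4.7% | about 2.3% |

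The protocol does not say which version it would use. If the only options are Fisher and the test on the four pre-specified strata, the error stays at or below 2.5%.

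**Step 4: stratifying on a 3-month change.** This is a deliberately extreme case: a binary marker changes in 20% on placebo and 80% on active treatment, and it alone drives response. With P(response) = a + b × marker, b = (0.60 − 0.20)/(0.80 − 0.20) = 0.667 and a = 0.20 − 0.667 × 0.20 = 0.067. The overall rates are then 20% and 60% as planned, but within each marker level the arms do not differ. Fisher's test has about 83% power. The Mantel-Haenszel test stratified on the marker rejects in about 1% of trials.

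**The case against.** Fisher's test is valid after stratified blocked randomisation. The protocol's stated purpose for the strata is balance, and the design delivers that. Nothing in the primary test inflates error, and in the settings that hold 20% against 60% overall it exceeds the planned 81%. **This stands:** the mismatch is one of efficiency and coherence, not bias.

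The power gains depend on assumed stratum rates. With a modest diet effect (15% against 25%) the gain is about one point; 3 to 5 points need a four- to nine-fold range. **This also stands**, though no setting showed a loss.

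The Mantel-Haenszel sentence sits in a paragraph on residual confounding and could be read as a supportive analysis. The text does not say that it replaces Fisher's test, nor that 3-month changes would define the strata; comparing them is a reasonable check on dietary change during the trial. **This stands in part:** the wording permits these uses and does not require them. But the sentence ties the test to evaluating the primary aim, and nothing excludes post-randomisation variables.

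Finally, the error exceeds .025 only with several candidate factors and an uncorrected statistic. **That is correct**, but the protocol limits neither.

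It cannot be set aside as a detail left to an analysis plan, because the protocol itself states the conditional choice. A later plan would have to override it.

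**Conclusion.** The concern holds, as something that should be fixed and not as a fatal flaw.

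- **Ignoring the strata** costs between nothing and about 5 points of power with the overall rates held at 20% and 60%, and up to about 10 points in the stronger alternative scenario. Stratum sizes and the prognostic strength of diet are assumptions throughout.
- **The undefined fallback** can raise one-sided error from .025 to about 4.7% if the best of Fisher and ten uncorrected one-factor tests is taken. It stays within .025 if a continuity correction is used.
- **Adjusting for a 3-month change** can in the extreme remove the treatment effect altogether (83% power to about 1%). The protocol allows this but does not mandate it.

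That the fallback is undefined and not limited to baseline variables is plain from the text and needs none of these assumptions.

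**What to change.** In section 13:

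1. Name one primary test per comparison in advance: the exact Mantel-Haenszel (conditional) test over the four randomisation strata, one-sided at .025. A pre-specified regression with stratum terms is an alternative. With only about 7 patients per arm per stratum (29/4), the exact version is preferable to the normal approximation. If cells are expected to be very sparse, fix beforehand a reduction to tomato intake for *IGF-1* and fish intake for *Cox-2*.
2. Keep the unstratified Fisher test as a sensitivity analysis, and state that the stratified test governs.
3. Delete the conditional clause.
4. State that any adjusted analysis uses only baseline variables named in advance, and that 3-month changes are reported descriptively by arm.

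The cost is wording only. No extra data are needed, and the sample size can stay at 29 per arm: the exact stratified test had at least 83% power in every setting enumerated in step 2, against the planned 81%.

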#### Interim Analysis:

An interim analysis for efficacy will be performed after 10 patients have been accrued to each of the 3 regimens and had the potential to be followed for 12 months from entry. With watchful waiting approximately 25% of patients will experience disease progression within 12 months of diagnosis. If more than 5 of the 10 patients on either supplement arm experience disease progression by 12 months from protocol entry, the study will be closed to further accrual. This will indicate that the 95% lower bound at 12 months is greater than 25% (30.4%). It is anticipated that this analysis will occur 15 months after the study is opened when approximately 45 patients have been entered on study. A statistician in the UCSF Comprehensive Cancer Center not associated with the design or final analysis will conduct this interim analysis.

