radiological or clinical - of metastasis), histologic (Gleason score  $\geq 8$  on the repeat biopsy), or biochemical (the three simultaneous conditions of PSA doubling time  $< 2$  years, final PSA  $> 8$  and  $p < 0.05$  on regression analysis of the time derivative of  $\ln$ PSA). In this study 137/206 patients remained on study without evidence of disease progression. Of the 69 patients who discontinued the study, only 36 (17%) had evidence of disease progression – 15 had clinical progression (5 underwent transurethral prostatic resection, and ten had an enlarging nodule on DRE), 16 had PSA progression and five had histologic progression. Of the remaining patients, 23 voluntarily withdrew, six were withdrawn for protocol violations, and four died of other causes. No patient had evidence of metastasis.

A second trial reported 23 month median follow-up of 98 men with inclusion criteria of Gleason score  $\leq 6$ , less than three of six biopsies containing cancer, no more than 50% involvement of any biopsy, and PSA density  $< 0.15$  ng/ml[60]. Patients were followed at yearly intervals with %free PSA and digital rectal exam. At two years, transrectal ultrasound was performed with 12-core diagnostic needle biopsy. Definitive treatment was recommended if Gleason pattern 8-10 histology was seen,  $> 2$  biopsies were positive for cancer, or if there was  $> 50\%$  involvement of any biopsy with cancer. Twenty-five of the 81 men (31%) had disease progression at two years. Of these men, 13 underwent radical prostatectomy and 12 of these men had potentially curable cancers ( $>70\%$  survival at 10 years expected based on pathologic features). The higher rate of progression seen in this trial was most likely an artifact of requiring only sextant biopsies, which allowed higher grade disease to be missed more often at the time of initial biopsy[61]. There was no difference in initial PSA, percent free PSA, PSA density or PSA velocity comparing patients with progression on re-biopsy to those without progression.

These data support the safety and feasibility of our proposed prostate cancer intervention trial. The articles cited demonstrate that definitive treatment for prostate cancer is possible at the first sign of progressive disease, and that with appropriate entry criteria, no man will be denied the opportunity for treatment with curative intent by participating in our study

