intervention arms are different in outcome, an analysis for efficacy will be performed after 10 patients have been accrued to each of the 3 treatments and followed for 12 months from study entry. If more than 5 of the 10 patients on either supplement arm experience disease progression at twelve months, the study will be closed to further accrual. It is anticipated that this analysis will occur 15 months after the study is opened when approximately 45 patients have been entered on study. A statistician in the UCSF Comprehensive Cancer Center not associated with the design or final analysis will conduct the interim analysis. Similar analysis will be performed when the trial has reached its total accrual goal.

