### **8.6 Study table: timing of physical exam, labs, transrectal ultrasound and biopsy**

The dietary intervention and molecular analysis will be complete within approximately three months for each patient. We anticipate that it will take up to three years to accrue the target number of patients and conduct the molecular analysis. Patients remaining on the watchful waiting protocol—regardless of assignment to control or intervention arms—will be followed indefinitely according to UCSF standard of care in the Urologic Oncology program.

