### **10.2 Assessment of safety**

#### **Assessment of Safety**

Toxicity is not expected in the MENS study, and since there is a stopping rule for efficacy, no patient should be harmed by participation in this protocol. Many of the past studies of omega-3 supplementation in humans studied coronary atherosclerosis using angiography. Despite cannulation of the arterial system after more than two years of 12-gram per day supplementation, no bleeding complications occurred in this study[70]. Likewise, there are no - expected side effects from lycopene supplementation[41].

Serum PSA and clinical progression will be monitored at visits approximately every three months.

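### The interim look's trigger and its forecast timing disagree: under steady accrual, 10 men per arm with 12 months' follow-up is reached near month 22–23 with about 62–66 of 97 enrolled, not at month 15 with 45

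*Protocol*

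**What the plan says.** The interim analysis is defined twice, in section 3.2.2.4 and under Interim Analysis in section 13. The section 13 text places it "after 10 patients have been accrued to each of the 3 regimens and had the potential to be followed for 12 months from entry"; section 3.2.2.4 sets the same count and the same 12 months. Allocation to the three regimens is "with equal probability" (section 4.6).

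The boundary is the same in both places. In section 3.2.2.4: "If more than 5 of the 10 patients on either supplement arm experience disease progression at twelve months", the study closes to further accrual. Section 13 adds that such a result puts the 95% lower bound at 30.4%, above the assumed 25%.

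Both places then give the same forecast: "It is anticipated that this analysis will occur 15 months after the study is opened when approximately 45 patients have been entered on study".

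Two other statements bear on this. Section 8.6 expects that "it will take up to three years to accrue the target number of patients" and to do the molecular analysis; the planned total is 97 (sections 4.4 and 13). Section 10.2 says that "since there is a stopping rule for efficacy, no patient should be harmed by participation in this protocol".

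**The concern.** A man has 12 months of follow-up at month 15 only if he entered by month 3. For 30 men to qualify, 30 must enter in the first three months, yet the same sentence expects only about 45 by month 15. The trigger and the forecast therefore describe different looks.

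The forecast tells an ethics or monitoring committee how much of the trial lies ahead when the rule is applied. The rule does nothing but close accrual, so its value depends on how many men have not yet entered. If the look comes later than stated, the rule protects fewer men than a reader would think, and section 10.2 gives this rule as the reason no patient should be harmed.

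**Working it through.** **Inputs**
- Trigger: 10 men × 3 arms = 30 men, each with 12 months since entry (sections 3.2.2.4 and 13). Equal allocation makes 30 the minimum.
- Forecast: month 15, about 45 entered (same sections).
- Planned total: 97 (sections 4.4 and 13). Accrual period: up to 36 months, including molecular analysis (section 8.6).
- No monthly rate is written. The forecast implies r = 45/15 = 3 per month.

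**The boundary figure reproduces.** Six of 10 has an exact one-sided 95% lower limit of 30.35%, matching the stated 30.4%. The boundary arithmetic is sound; the problem is the timing.

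**Status at month 15.** Men with 12 months of follow-up = r × (15 − 12) = 3 × 3 = 9, about 3 per arm. A count out of 10 per arm is not available.

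**When the trigger is met.** With uniform accrual and no pause (none is described):
- time of look = 30/r + 12
- enrolled at look = r × (30/r + 12) = 30 + 12r

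| Accrual assumption | r per month | 30th man | Look | Enrolled | Still to enter (of 97) |
|---|---|---|---|---|---|
| 45 in 15 months | 3.00 | month 10.0 | month 22.0 | 66 | 31 |
| 97 in 36 months | 2.69 | month 11.1 | month 23.1 | 62 | 35 |
| 97 in 33 months (3 months kept for the last intervention) | 2.94 | month 10.2 | month 22.2 | 65 | 32 |
| 97 in 24 months (assumed faster) | 4.04 | month 7.4 | month 19.4 | 78 | 19 |

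At the stated 45, the number still to enter would be 97 − 45 = 52. Faster accrual brings the look forward but leaves fewer men to spare.

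**Can either stated number hold alone under uniform accrual?**
- Month 15: 30/r + 12 = 15 gives r = 10 per month. All 97 would then be enrolled by month 9.7, before the look.
- 45 enrolled: 30 + 12r = 45 gives r = 1.25 per month. The look would fall at 30/1.25 + 12 = month 36.

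**What would fit both?** Either 30 men in the first 3 months and then 15 in the next 12 (10 per month falling to 1.25), or a trigger of 10 men in total: 10/3 + 12 = month 15.3 with 46 enrolled. The second is close enough to suggest how the forecast arose, but it is not the trigger written.

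**Randomization detail.** Stratified blocks of 9 do not guarantee 10 per arm at the 30th man. A simulation assuming four equally likely strata needed about 32.6 men on average, giving about month 22.9 with about 69 enrolled at 3 per month. This moves the look slightly later.

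**What the rule can detect.** The binomial probability of at least 6 progressions among 10 men, per arm, is:
- 2.0% at a true 12-month rate of 25%
- 17% at 40%
- 38% at 50%

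A doubling of the assumed rate on one arm would be missed about 62% of the time (1 − 0.38).

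**The case against.** The strongest reply is that the month and enrolment are a forecast, hedged as such. The operative trigger and boundary agree in both sections, and no decision depends on the month. That stands: the rule can be run as written. But the forecast is the protocol's only statement of when the rule acts and how far enrolment has gone, and it is wrong under any roughly steady accrual.

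A second reply is that the rate is inferred and that three years is an upper limit which includes laboratory work. That also stands. The contradiction is therefore conditional on roughly uniform accrual and is not a logical impossibility. Sharply front-loaded entry would satisfy both figures, but nothing in the protocol suggests it.

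Four stronger readings are tempting and are not supported:
- **That this is the only protection patients have.** Sections 9.4 and 12 remove individual men on progression, section 10.2 has PSA and clinical progression checked about every three months, and section 10.1 provides committee safety review. The rule is only the sole trial-level stopping rule with a numerical boundary.
- **That the timing error is why most enrolled men will have finished the supplement by the look.** At 3 per month this is already so at month 15 (45 − 9 = 36 of 45, 80%), against 66 − 9 = 57 of 66 (86%) at month 22. It follows from a 12-month endpoint after a 3-month intervention.
- **That the 25% benchmark is too high, given the cohorts in section 2.5.** Those cohorts defined progression differently. The first required Gleason 8 or more for histologic progression, whereas section 9.4 here counts a sum of 7 or more (with a microfocus exception) and core-involvement criteria. For the second, "Twenty-five of the 81 men (31%) had disease progression at two years", but the protocol attributes its higher rate to sextant sampling at entry. Converting either figure to a 12-month rate needs assumptions the protocol does not give.
- **That a fixed benchmark and small numbers are errors in themselves.** They are design choices. Section 3.2.2.3 concedes low power for progression, and section 13 plans a log-rank comparison with placebo.

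**Conclusion.** The point holds as an internal contradiction in sections 3.2.2.4 and 13. Assuming roughly uniform accrual at the implied 3 per month, which is consistent with 97 men in up to three years, the trigger as written is met at about month 22–23 with about 62–66 of 97 enrolled. About 9 men, not 30, would qualify at month 15. The rule could then keep about 31 to 35 planned men from entering, not 52.

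Section 10.2's inference that the rule means no patient should be harmed does not follow. The rule comes later than stated, acts only on accrual, and has a 38% chance per arm of triggering when the 12-month rate is 50%. Calling it an efficacy rule obscures that its one boundary is for excess progression on a supplement. Sample size and the primary analysis are unaffected.

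**What to change.** 1. Reconcile sections 3.2.2.4 and 13. Either keep the trigger and restate the forecast as about month 22–23 with about 62–66 men entered, giving the accrual assumption; or, if a look at month 15 is intended, change the trigger. The second option needs a new boundary, because with about 3 men per arm at 12 months a count out of 10 cannot be used.
2. Describe the rule in both sections and in section 10.2 as one for excess progression on a supplement arm.
3. State its operating characteristics beside the 30.4% bound: per-arm probability of triggering 2.0% at a 25% rate, 17% at 40% and 38% at 50%.
4. Remove from section 10.2 the inference that the rule means no patient should be harmed, and refer instead to the safeguards already in sections 9.4, 10.1, 10.2 and 12.

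Keeping the trigger costs wording only, in three places. The price is that the stated protection becomes less favourable: about 31 to 35 men who could still be spared instead of 52. Changing the trigger also costs the work of setting and justifying a new boundary.
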